### Power analysis

This RCT is powered only to detect intervention effects on symptoms of CMDs, as measured by the SSQ-14, which is the primary outcome. All other quantitative outcomes—including other mental health measures, HIV engagement indicators, and psychosocial variables—will be treated as exploratory and used to inform effect size estimates and future trial design. With the proposed sample size of 126 participants (63 per arm) and using a two-sided alpha level of 0.05, the study will have 80% power to detect a medium effect size of Cohen’s *d* = 0.5 in SSQ-14 scores, which will be analyzed as a continuous outcome. This is a conservative estimate, selected to reflect a clinically meaningful but smaller effect than that observed in the original Friendship Bench trial, which reported a large effect (*d* ≈ 0.75–0.8) over a 6-month period. Accounting for 30% attrition, the sample size estimate was adjusted to account for an original sample size of 180 participants (90 per group). Since our study primarily measures outcomes at 3 months, a smaller effect size is assumed to avoid overestimating power. Between-group comparisons will be conducted at the 3-month follow-up, prior to the waitlist control group receiving the intervention. At 6 months, only within-group analyses will be conducted to assess sustained changes in the intervention group and pre-post change in the waitlist control group. No between-group comparisons will be performed at 6 months.

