*Composite HIV engagement scores*: To simplify analysis and reflect multiple components of HIV prevention and treatment engagement, we will construct composite engagement scores for each group (based on HIV status). Composite scores will be created by assigning a binary value (e.g., 0 = no, 1 = yes) to multiple related indicators of HIV engagement, then adding the values together to generate a single continuous score. These composite scores will be analyzed as exploratory outcomes, included as covariates in models predicting mental health outcomes, and used to test for interaction effects with intervention group to explore potential moderation.For HIV treatment engagement (among participants living with HIV), the following indicators will be composited into a single score:◦ Self-reported clinic attendance;◦ ART initiation and adherence;◦ HIV viral load documentation;◦ HIV treatment self-efficacy (via HIV-SE).◦ Each indicator will be scored and summed to create an overall treatment engagement score.◦ Higher scores reflect stronger engagement in HIV care.For HIV prevention engagement (among HIV-negative or status-unknown participants), the following indicators will be composited:◦ Consistent condom use;◦ PrEP uptake or readiness;◦ Reduction in HIV risk behaviors (via WAF);◦ HIV prevention self-efficacy/readiness (via HPRM).◦ Higher scores reflect stronger engagement in HIV prevention strategies.

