*Moderation and mediation analyses (exploratory)*: Post hoc exploratory analyses will assess whether changes in mental health outcomes mediate or moderate the intervention’s effects on HIV-related outcomes. Mental health change scores will be calculated separately for each follow-up period (i.e., 3 months and 6 months post-intervention) by subtracting baseline values from the respective follow-up values. This will allow us to assess both short-term and sustained mental health changes and explore their relationship with HIV-related outcomes over time.Mediation: We will test whether changes in CMD symptoms (SSQ-14), depression (PHQ-9), anxiety (GAD-7), or PTSD (CPSS) symptoms help explain (mediate) observed changes in HIV prevention or treatment outcomes using causal mediation models.Moderation: We will include interaction terms between changes in mental health symptoms and intervention group to assess whether the impact of the intervention on HIV outcomes differs depending on mental health changes. Additionally, we will explore whether baseline levels of early adversity (measured by the Adverse Childhood Experiences International Questionnaire; ACE-IQ) [64], social support (measured by the Oslo social support scale; OSSS-3) [66], and coping self-efficacy (measured by the Coping Self-Efficacy scale; CSE) [65] moderate the relationship between the intervention and mental health or HIV outcomes.

*Adjustment variables and stratified analyses:* HIV status (positive vs. negative/unknown) will be included as a covariate in pooled models to adjust for baseline differences. Stratified analyses by HIV status will be considered if each group has a sufficient sample size to support reliable subgroup modeling (e.g., ≥ 40 participants per group). Given the small overall sample size (*N* = 90, accounting for 30% attrition), such stratified analyses may be underpowered and are therefore considered exploratory and hypothesis-generating only. All models will follow an intention-to-treat (ITT) framework, and statistical significance will be assessed at a two-sided *α* = 0.05, with 95% confidence intervals reported. Non-adherence will be handled by analyzing all participants as randomized (ITT); we will also run a pre-specified per-protocol sensitivity analysis defined as completion of ≥ 4/6 sessions and no major protocol deviations. Missing data will be addressed using mixed-effects models, which provide valid estimates under missing-at-random assumptions.

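### Three exploratory analyses (arm-by-symptom-change moderation, HIV composites as covariates, and 6-month change scores in mediation) are specified in a way that breaks the randomised comparison

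*Protocol article*

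**What the plan says.** All three specifications are in the Quantitative data analysis section of the protocol article.

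- **Moderation.** "We will include interaction terms between changes in mental health symptoms and intervention group". The stated purpose is to see whether the intervention's impact on HIV outcomes depends on how symptoms changed. The same paragraph also plans moderation by baseline ACE-IQ, OSSS-3 and CSE.
- **Mediation.** Changes in SSQ-14, PHQ-9, GAD-7 or CPSS are to explain "observed changes in HIV prevention or treatment outcomes using causal mediation models". The sentence names no time point. The introduction to the same paragraph says: "Mental health change scores will be calculated separately for each follow-up period", naming 3 and 6 months, so that short-term and sustained changes can be related to HIV outcomes.
- **Composites.** The HIV engagement scores are analysed as outcomes and are also "included as covariates in models predicting mental health outcomes, and used to test for interaction effects with intervention group". No time point is given. One listed prevention component is "Reduction in HIV risk behaviors (via WAF").

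The Study outcomes section limits 6-month analysis to within-group change because both arms will have received the intervention by then. The Power analysis section repeats this: "No between-group comparisons will be performed at 6 months". The mediation and moderation analyses are labelled post hoc and exploratory.

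**The concern.** Randomisation makes the arms comparable at baseline. It does not make women with the same later symptom change, or the same later HIV engagement, comparable between arms. A model that conditions on such a variable and then reads the arm coefficient or an arm interaction as an intervention effect has left the randomised comparison.

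The assumed causal direction is also inconsistent. The Hypothesis section has the intervention reducing depressive symptoms, which then improves HIV engagement. The composite paragraph adjusts mental health outcomes for that engagement, which on the plan's own hypothesis lies downstream of them. Symptom change, meanwhile, is both mediator and moderator of the same effect.

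What is at stake is the mechanism evidence. The Abstract says the data will inform hypotheses about mental health as a mediator of HIV outcomes, and the Conclusion expects the results to inform larger trials. The primary result is not at stake.

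**Working it through.** **The plan's own figure.** The disputed analyses have no stated figure. The powered one reproduces: d = 0.5, two-sided alpha 0.05 and 80% power give 2 × (1.960 + 0.842)² / 0.5² = 62.8, so 63 per arm. Then 126 / 0.7 = 180. Nothing below changes these numbers.

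**1. Conditioning on symptom change (HIV outcome models).** Take d = 0.5 on symptoms (the plan's figure), no true effect of arm on the HIV outcome, and an unmeasured common cause of symptom change and HIV outcome with loading c on each, in opposite directions (an assumption). On standardised scales the within-arm slope of outcome on change is -c², so the arm coefficient adjusted for change is 0 - (-c²)(-0.5) = -0.5c². A simulation with 63 per arm and 1,500 runs per scenario agrees:

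| c | -0.5c² | Simulated | Rejection rate |
|---|---|---|---|
| 0 | 0 | 0.00 | 4.5% |
| 0.3 | -0.045 | -0.05 | 6% |
| 0.5 | -0.125 | -0.13 | 12% |
| 0.7 | -0.245 | -0.24 | 31% |

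The unadjusted arm contrast stayed at about 0.00, with about 5% rejection.

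The arm-by-change product term is spurious only when the common cause acts on symptom change differently in the two arms. With c = 0.5, and the common cause acting on symptom change in the control arm only, the slopes are -0.25 (control) and 0 (intervention). The product term is then 0.25, rejected in 25% of runs. In milder scenarios rejection was 5-7%.

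**2. Composite as covariate (mental health models).** In a linear model, adjustment moves the arm coefficient by within-arm slope × effect of arm on the covariate. The documents give neither input, so both are assumptions:

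| Slope | Effect 0 | Effect 0.3 SD | Effect 0.5 SD |
|---|---|---|---|
| 0.2 | 0 | 0.06 | 0.10 |
| 0.4 | 0 | 0.12 | 0.20 |

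**3. Mediation at 6 months.** Assume true mediation with a symptom-to-outcome slope of -0.4 and a gain of 0.5 SD from treatment. The arm-based indirect effect is the arm difference in symptom change × slope.

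- At 3 months: -0.5 × -0.4 = 0.20.
- At 6 months the waitlist arm has also gained 0.5.
  - Early arm keeps its full gain: 0 × -0.4 = 0.
  - It keeps half: (-0.25 + 0.5) × -0.4 = -0.10.
  - It keeps none: 0.5 × -0.4 = -0.20.

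The simulation gave 0.20, 0.00, -0.10 and -0.20. Mediation is real in every case, yet at 6 months the arm-based estimate vanishes or reverses sign.

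**The case against.** The case on the other side is substantial and narrows the point.

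- **Most Aim 3 models are sound.** A reader might infer that Aim 3 as a whole cannot be read as intervention effects. The documents do not support that. Most Aim 3 outcomes get ordinary mixed models with the arm comparison at 3 months, and ACE-IQ, OSSS-3 and CSE are proper baseline moderators.
- **The primary analysis is untouched.** Setting 0.06 to 0.20 SD against the SSQ-14 design effect of 0.5 would suggest that the primary result is at risk. The listed terms of that model are a random intercept, time, group and their interaction, with no composite. The two composites also differ by HIV status, so neither is a common covariate for a pooled model.
- **The shift may be zero.** The Description of the intervention section cites a trial of the parent intervention with no significant impact on ART adherence or viral suppression. Where engagement lies on the causal pathway, part of the shift is a change from total to direct effect and not bias.
- **Most composite items can be measured at baseline.** Clinic attendance, condom use, PrEP use, HIV-SE and HPRM can all be taken then. Among the prevention components, only the reduction in risk behaviour needs follow-up by its nature.
- **Arm-based mediation at 6 months is inferred.** The mediation sentence names no time point, and a within-group association at 6 months would respect the plan's restriction.
- **Mediation needs a post-randomisation mediator.** Three-month causal mediation is not invalid on that ground. It rests on there being no unmeasured mediator-outcome confounding.

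What remains is the wording as written. The group-by-change term is explicitly said to assess the intervention's impact, the covariates are not limited to baseline, and the 6-month change scores carry no restriction. A within-group reading at 6 months would also leave a causal mediation model with no exposure contrast. The exploratory label lowers the weight of the point but does not make these estimates interpretable as intervention effects.

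**Conclusion.** The concern holds for three exploratory analyses only.

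1. The group-by-symptom-change term does not estimate effect modification. This follows from the text and needs no numerical assumption. How misleading it would be depends on unmeasured common causes, and in most of the scenarios tried the product term itself was rejected near the nominal rate.
2. Mental health models adjusted for a post-baseline HIV composite can have a changed or biased arm effect. The shift is zero if engagement is unaffected, and 0.06 to 0.20 SD under the assumed slopes and effects.
3. The 6-month change scores leave room for an arm-based mediation analysis that the Study outcomes and Power analysis sections exclude. That it would be run by arm is a firm inference, not a statement in the text. If it were, the estimate could be null or reversed although mediation is real.

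The sample size, the primary estimate, the plain 3-month comparisons and the baseline moderators stand. The wording should be corrected before analysis.

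**What to change.** Reword three places in the Quantitative data analysis section.

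- **Moderation:** use only baseline moderators, for example baseline SSQ-14 or PHQ-9, ACE-IQ, OSSS-3 and CSE. Drop the group-by-change models, and let the causal mediation model carry any exposure-mediator interaction.
- **Mental health models:** allow only baseline HIV variables as covariates or moderators, namely HIV status and engagement items that can be measured at baseline. Keep the follow-up composites, including the reduction in risk behaviour, as outcomes.
- **Mediation:** run arm-based mediation only on the randomised 0-3 month contrast. Report any 6-month change-score association as within-group and non-causal.

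This costs a wording change and fewer exploratory models. It needs no new data and no change in sample size.

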### Randomization

We will use permuted block randomization, stratified by HIV status, to ensure balance across study arms. The randomization sequence will be computer-generated using REDCap’s randomization module. REDCap will conceal allocation until after baseline data entry is complete, ensuring that research staff cannot foresee or manipulate assignments. The study biostatistician will generate the allocation sequence and upload it into REDCap. The research assistants will enroll participants, and REDCap will automatically assign the participant to their group after enrollment and baseline data completion. Participants will be randomized 1:1 to the intervention group (offering intervention sessions from 0 to 3 months) or the waitlist control group (offering intervention sessions from 3 to 6 months), with up to six sessions delivered over 3 months among both arms.

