### Quantitative data analysis

We will use descriptive statistics to summarize participant characteristics at baseline, feasibility and acceptability metrics, and other implementation outcomes. To assess baseline differences between participants who complete the intervention and those who drop out, we will conduct bivariate comparisons using independent samples t-tests or Wilcoxon rank-sum tests for continuous variables and chi-square or Fisher’s exact tests for categorical variables.

*Primary outcome analysis (powered):* To assess the effect of the adapted intervention on symptoms of CMDs (SSQ-14), we will use mixed-effects linear regression models. This is the only outcome for which the study is statistically powered, based on detecting a standardized mean difference of Cohen’s d = 0.5 at the 3-month follow-up. The model will include:A random intercept for participants to account for within-subject correlation from repeated measures;A fixed effect for time (baseline vs. follow-up);A fixed effect for study group (immediate intervention vs. delayed control);A group × time interaction term to estimate the differential intervention effect over time.

If the model assumptions (e.g., homoscedasticity, normally distributed residuals) are not met, we will consider using generalized linear mixed models with appropriate link functions and distributional assumptions to reduce the risk of Type I and Type II errors.

*Exploratory analyses:* All other outcomes will be analyzed using mixed-effects linear, logistic, or ordinal regression models, depending on the outcome type. These outcomes include:Mental health outcomes: depression (PHQ-9; binary and continuous), anxiety (GAD-7; continuous), and PTSD (CPSS; continuous) symptoms;HIV prevention outcomes (among HIV-negative or status-unknown participants): consistent condom use, PrEP uptake or readiness, HIV risk behaviors (via WAF), and HIV prevention self-efficacy/readiness (via HPRM);HIV treatment outcomes (among HIV-positive participants): ART adherence, clinic attendance, viral load documentation (if available), and HIV treatment self-efficacy (via HIV-SE);

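### HIV status, the stratification factor, is entered only as a time-constant covariate, which does almost nothing for the group × time effect; HIV status × time should be added

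*Protocol article*

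**What the plan says.** The Randomization section names one stratification factor: "We will use permuted block randomization, stratified by HIV status, to ensure balance across study arms".

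Under Quantitative data analysis, the primary SSQ-14 model is a linear mixed model with these terms:
- "A random intercept for participants to account for within-subject correlation from repeated measures";
- fixed effects for time (two levels, baseline and follow-up) and for study group;
- "A group × time interaction term to estimate the differential intervention effect over time".

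Baseline is therefore a row of the outcome, and the interaction carries the treatment effect. That list has no HIV term. The paragraph on adjustment variables, later in the same section, supplies one: "HIV status (positive vs. negative/unknown) will be included as a covariate in pooled models to adjust for baseline differences". No HIV status × time term is stated. The same paragraph relies on the mixed model, under missing at random, for missing data. The Power analysis section expects 30% attrition, so some women will contribute a baseline score only.

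**The concern.** A covariate that is constant over time shifts a woman's baseline and 3-month scores by the same amount. The group × time term compares changes between arms, so the shift largely drops out of it. The stated adjustment can therefore do little for the one effect the trial is powered on.

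Two things are at stake. If women with and without HIV change differently by 3 months, that difference stays in the residual and the reported standard error is wider than it need be. If dropout also depends on HIV status differently in the two arms, the model cannot represent the difference in change, and the effect estimate is biased although HIV status is in the model.

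The stated purpose is also off target. Stratification already makes HIV status nearly balanced at baseline; the reason to adjust is that the design stratified on it.

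**Working it through.** **1. The plan's own figure.** The Power analysis section gives its basis: "With the proposed sample size of 126 participants (63 per arm) and using a two-sided alpha level of 0.05". The target there is 80% power at d = 0.5. Per arm, n = 2(1.960 + 0.842)²/0.5² = 62.8, so 63. Power at 63 per arm is 80.1% (normal approximation). 63/0.7 = 90 per arm, 180 in all. The figures reproduce and do not depend on this point.

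**2. Why the covariate cancels.** With G = group, H = HIV status and t = 0 or 1, the plan's model is Y = b0 + b1·G + b2·t + b3·G·t + γ·H + u + e. For a woman with both scores, the change is D = b2 + b3·G + (e1 − e0). Both γ·H and u are gone. With complete pairs the estimate of b3 is the between-arm difference in mean D, with or without H. In simulated complete data the estimate differed by 0.00000 and the standard-error ratio was 1.00000 in every run.

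**3. Precision lost with complete data.** Assumptions not in the documents: proportion HIV-positive p = 0.30, within-person correlation ρ = 0.5, and women with HIV improving δ SD less. Within HIV strata, var(D) = 2(1 − ρ) = 1. Without H × t the model treats δ as noise, so the reported standard error is too wide by the ratio r = √(1 + p(1 − p)δ²) = √(1 + 0.21δ²). Stratification keeps δ out of the real sampling error, which stays at √(2/63) = 0.178. The test therefore rejects beyond 1.96·r true standard errors. Type I error is 2Φ(−1.96r) and power is Φ(0.5/0.178 − 1.96r).

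| δ (SD) | r | Type I error | Power |
|---|---|---|---|
| 0 | 1.000 | 5.0% | 80.1% |
| 0.2 | 1.004 | 4.9% | 79.9% |
| 0.3 | 1.009 | 4.8% | 79.6% |
| 0.5 | 1.026 | 4.4% | 78.7% |
| 0.8 | 1.065 | 3.7% | 76.4% |

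The formula assumes exact balance of HIV status. Simulation with permuted blocks within strata gives about 4.5% and 3.9% type I error in the last two rows, and power losses of about 1.5 and 4 points.

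**4. Attrition unrelated to HIV status or arm (180 enrolled, 30% lost).** Baseline-only women bring between-person information into the interaction, so the covariate no longer cancels exactly. With an HIV effect on level of 0.5 SD, it moves the estimate by 0.009 SD on average and multiplies the standard error by 0.998 (0.993 at 1.0 SD). If HIV status also shifts the change by 0.5 SD, the standard errors are 0.1754 (no HIV term), 0.1751 (covariate) and 0.1711 (HIV status × time).

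**5. Attrition that depends on HIV status and arm.** Take 50% loss among women with HIV and 20% among the others in the intervention arm, and 30% throughout the waitlist arm; the true effect is 0.50.
- Hand check. The HIV-positive share of those followed up in the intervention arm is 0.3 × 0.5/(0.3 × 0.5 + 0.7 × 0.8) = 0.15/0.71 = 0.211, against 0.30 in the waitlist arm. In an analysis of completers' changes the bias would be (0.30 − 0.211) × δ = 0.044 at δ = 0.5 and 0.071 at δ = 0.8.
- Mixed model with the HIV covariate, simulated: 0.537 and 0.558, a bias of about 0.04 to 0.06. The same bias appears when the true effect is zero. With HIV status × time: 0.50 and 0.00.
- HIV status affecting level only (0.5 SD): about 0.48 or 0.52 without any HIV term, depending on the direction of the level effect, and 0.50 with the covariate.
- Milder pattern (40% against 26%, δ = 0.5): bias of about 0.02. The same HIV-related loss in both arms: essentially none.

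**The case against.** A reader might infer that the stated adjustment has no effect on the primary result at all. The documents do not support that. Exact cancellation needs complete pairs and the linear model. The plan expects 30% attrition and keeps baseline-only women in the likelihood, and in that setting the plain covariate does useful work when HIV status affects level only. Nor is cancellation exact in the logistic and ordinal models or in the generalized linear fallback.

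A reader might also infer that the missing-at-random assumption fails. It does not. Dropout that depends on arm and HIV status, both observed, is still missing at random; what fails is the mean model, which omits the difference in change.

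The size of the harm rests on an effect the article does not give. A 0.5 SD difference in change by HIV status is as large as the treatment effect the trial is powered for. Smaller differences cost almost nothing, and the complete-data error is conservative rather than a source of false positives. The bias scenario needs a strong, arm-specific dropout pattern, and even then the bias is about a third of the standard error (0.17 to 0.18) or less.

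Finally, the exact form of a covariate is often left to an analysis plan, and the article does not exclude a time interaction. That tempers the point. It does not remove it: the article lists the model terms, states the form in which HIV status enters, and gives a reason for adjusting that does not match the design.

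**Conclusion.** The point holds as a modest, low-cost improvement. In the linear model with complete data, the covariate as stated leaves the group × time estimate and standard error unchanged. With the planned attrition it adds under 1% in precision on average, and it protects against differential dropout only through the level of SSQ-14.

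Under the assumed 30% HIV-positive and correlation 0.5, the cost ranges from nothing (no HIV effect on change), through a standard error 1% or less too wide and a power loss under 1 point (0.2 to 0.3 SD), to a standard error 3% to 7% too wide (0.5 to 0.8 SD). Bias of 0.04 to 0.06 SD arises only if, in addition, dropout differs strongly by HIV status in one arm. The documents neither establish nor rule out these conditions. They do not show that the primary analysis is invalid or that the sample size is wrong.

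**What to change.** In the primary-model list and in the adjustment paragraph of Quantitative data analysis, state that the SSQ-14 model includes HIV status and HIV status × time. Do the same for the other pooled linear group × time models. Give the stratified randomisation as the reason for adjustment, in place of baseline differences.

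Modelling the 3-month score directly with HIV status as a covariate is not an equivalent substitute: it drops women who have only a baseline score and is a different estimator.

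The cost is one fixed-effect term, with no new data and no extra participants. Where the term is not needed, the standard error is essentially the same under random attrition (0.1711 against 0.1709). With strong differential dropout running in opposite directions in the two arms, it is about 1.5% larger (0.1740 against 0.1715).
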